
### Objectives and Outcomes

We will evaluate the efficacy of the psychological intervention (PIPCI) manual in an RCT comparing the intervention with both an active control group condition (cognitive training), and a waiting list control group condition. The primary objective is to evaluate intervention-related changes in psychological flexibility measured with the second version of the Acceptance and Action Questionnaire (AAQ-II) (Bond et al., 2011). The secondary objectives are to further evaluate intervention-related changes with measures of psychological health, cognitive measures and biological markers (obtained from blood and saliva). The behavioral measures will also be evaluated in relation to changes in biological markers (obtained from blood and saliva; see section “Materials and Methods” for further information). We will also evaluate how the participants experience the intervention, and how they handle preventive actions, using qualitative methods.

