**Phase 5: Closure**		
10	Summary and closure	A summary of the intervention is done, including reflections on closure and a discussion of questions that the patient may have. Also, a plan for relapse prevention is discussed and formulated, including the need for repetition and use of strategies to handle discomfort in the future.•Group 2, active control condition: Computer-based training tasks administered with a difficulty level adapted to patient performance. The cognitive training method that will be used targets executive control (i.e., ability to coordinate thoughts and actions in accordance with internal goals) (Miyake et al., 2000). The tasks are intended to train specific types of executive functions: “Shifting” (flexibly switching between different stimuli), “Updating” (organizing information in working memory and actively exchanging old information with new) and “Inhibition” (actively inhibiting an automatic or more dominant response). An active control group is important to include to create a placebo-like condition in addition to the waiting list condition (Van De Ven et al., 2016). It is important that the participants believe that they will improve to facilitate motivation, attention, or other factors that will increase performance as well. In addition, the active control group will receive the same amount of sessions as the experimental group, thus the active control group also consists of 10 sessions (55 min per occasion), once a week. On those occasions, the patient will meet a psychologically trained (i.e., psychology student under clinical training or with an MSc in psychology) research assistant that coaches the patients during the cognitive training. Between sessions, patients are supposed to take two walks (45 min per occasion to meaningfully match the home exercises in the experimental group). Reminders will be sent to the patient’s mobile telephone via SMS.•Group 3, waiting list condition: This group only receives regular health information that is provided after the extended cognitive examination at the Cognitive Center. After the finalization of the post-intervention evaluations, this group will be offered to participate in one of the active interventions by their preference. We will conduct additional post-intervention assessments also for those individuals in this group that accept this offer to increase the power of the intervention evaluation.

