### Power Estimation and Sample Size

No studies are available directly comparing CBT/ACT in a cognitively impaired population with an active control condition using AAQ-II. Therefore, we designed our RCT as a superiority trial with enough statistical power to detect a difference in outcome between treatments (if present) with a medium effect size. We chose this minimum difference because such a difference is important based on a patient’s perspective or clinical knowledge. Expecting larger differences in outcome does not seem realistic (Regan and Varanelli, 2013) and might result in an underpowered study while detecting smaller differences is of less relevance for clinical practice. The calculation is estimated on AAQ-II pre- and post-intervention change between the PIPCI group and the active control group Sample size was calculated with the R package SIMR, which allows power calculations of Linear Mixed Models (LMM) and is based on Monte Carlo simulations (Green and Macleod, 2016). The sample size estimate is based on changes in our primary outcome, AAQ-II. The model included the interaction of time (pre- versus post-test 1; continuous) and group (experimental versus active control; factor). The model also had a subject ID (factor) as a random effect to account for repeated measurements. We used the power curve function to explore trade-offs between power and sample size. The analysis showed that to get a significant difference between the experimental group and the active control group we need at least 35 participants (to have 93% power) in each group. We expect a 15% attrition rate (Norton et al., 2014), so initial recruitment of 120 (40 in each group) participants should ensure that about 105 participants remain in the final sample. The output of the power analysis is shown in Figure 3.

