### Statistical Analysis

#### Strategy for the Main and Secondary Hypotheses Analyses

The continuous longitudinal data derived from the RCT will be analyzed using appropriate growth models (e.g., LMM) that in addition to studying change at the group level also can: model change on the individual level; flexibly incorporate time-varying predictors; handle dependency for repeated observations and provide correct estimates with missing data under largely unconstrained missing data conditions (Hesser, 2015). As a default strategy we will use LMM to analyze the condition by time interaction and will follow established recommendations for model specification and reporting results (Bolger and Laurenceau, 2013). In the main analysis, we will compare intervention change between the PIPCI group and the active control group. However, we will also compare the PIPCI group and the active control group with the waiting list group. An alpha level of 0.05 and a 95% CI will be used to evaluate the main and secondary analyses. Regarding the LMM-analyses, assumptions relating to the normal distribution of residuals and homogeneity of variance will be assessed, respectively, based on visual evaluation of a histogram of model residuals, as well as by a plot of the model fitted values against the residuals from the model.

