#### Sensitivity Analyses

Importantly, in line with the intention-to-treat principle, all available randomized participant data will be analyzed using maximum likelihood estimation, an approach that uses information from all available observations to estimate parameters and provides unbiased estimates and standard errors in the presence of incomplete data under the assumption that data are missing at random. Appropriate sensitivity analyses will be performed to assess the robustness of the findings, and to identify possible key limitations, e.g., the effects of dropout.

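### Follow-up of waiting-list patients who choose a treatment is meant to raise the power of the evaluation, and nothing keeps these non-randomised data out of the randomised contrasts

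*Protocol article*

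**What the plan says.** The description of the waiting-list arm closes the RCT Design and Groups section, after Table 1. It says: "After the finalization of the post-intervention evaluations, this group will be offered to participate in one of the active interventions by their preference". For those who accept, the protocol plans "additional post-intervention assessments also for those individuals in this group that accept this offer to increase the power of the intervention evaluation".

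The only efficacy evaluation described is the randomised one. Objectives and Outcomes states: "We will evaluate the efficacy of the psychological intervention (PIPCI) manual in an RCT comparing the intervention with both an active control group condition", with the waiting list as second comparator. The statistical strategy says: "In the main analysis, we will compare intervention change between the PIPCI group and the active control group". It adds that both active groups will also be compared with the waiting list. Sensitivity Analyses says that "in line with the intention-to-treat principle, all available randomized participant data will be analyzed using maximum likelihood estimation".

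Neither the statistical strategy nor Sensitivity Analyses mentions data collected after a waiting-list patient has started treatment. The main hypothesis covers superiority over both controls and persistence of the effect at 6 months.

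**The concern.** The sentence gives a purpose for the extra assessments, and that purpose has a statistical meaning. Observations raise the power of a comparison only if they contribute to its estimate. Read naturally, waiting-list patients who later take PIPCI would be counted with the PIPCI arm, and those who take cognitive training with the active control arm.

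They are not exchangeable with the patients randomised to those arms:

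- They choose their treatment. The protocol treats expectancy as a threat: it withholds from participants which intervention is the experimental one, and it says that belief in improvement matters.
- They start about 12 weeks later: 10 weeks of intervention plus the one-week margins before and after it.
- They have already been assessed twice, which matters most for the cognitive secondary outcomes.

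In the waiting-list comparisons the same people would also supply both untreated and treated observations. At stake is whether the p-values and intervals for efficacy still rest on randomisation. The Discussion section relies on the control condition for its causal conclusions.

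**Working it through.** **1. The plan's own power.** The protocol states 93% power with 35 per group for PIPCI versus active control. The numerical effect, SD and pre-post correlation given to the simulation are not reported, so the figure can be matched only conditionally. Assume a medium effect of 0.5 outcome SD, two-sided 5% (implied by the 95% CI), and a correlation rho near the quoted AAQ-II test-retest range of 0.79 to 0.81.

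- Change-score SD = sqrt(2(1 − rho)): power is 89.8%, 91.1% and 92.4% at rho = 0.79, 0.80 and 0.81.
- Baseline-adjusted SD = sqrt(1 − rho²): power is 92.7%, 93.7% and 94.6%.

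So 93% is reachable at rho of about 0.8. It corresponds to a standardised difference of (1.960 + 1.476)/sqrt(35/2) = 0.82 SD of change.

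**2. What crossovers would add nominally.** Attrition of 15% leaves 40 × 0.85 = 34 waiting-list patients. Adding them to 35 + 35, at 0.82 SD of change, gives these powers:

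- 17/17 split (52 versus 52): 98.7%.
- All choosing one arm (69 versus 35): 97.7%.

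Without them, power is 93% at 35 per arm. At 34 per arm it is Φ(0.82 × sqrt(34/2) − 1.96), about 92%.

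**3. Bias in PIPCI versus active control if they are pooled.** Let b be the shift in change among crossovers who chose PIPCI, m1 of them, with no shift in those choosing cognitive training. The bias is b × m1/(35 + m1). The documents give no value for b, so all values here are assumptions. Type I error comes from 20,000 simulated two-sample t-tests with no true effect and b in SDs of change:

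| Split (PIPCI/training) | b = 0 | b = 0.2: bias | b = 0.2: type I error | b = 0.3: type I error |
|---|---|---|---|---|
| 17/17 | 5.0% | 0.065 SD | 6.1% | 7.8% |
| 27/7 | 5.0% | 0.087 SD | 7.0% | 9.2% |
| 34/0 | 4.8% | 0.099 SD | 7.7% | 11.2% |

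**4. Extreme case with the shift in outcome SDs.** Take 34 randomised patients per arm and all 34 crossovers choosing PIPCI.

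- Bias = 0.5 × b.
- SE = sqrt(2(1 − rho)) × sqrt(1/68 + 1/34).
- b = 0.2, rho = 0.5: SE = 0.210, bias/SE = 0.476, P(|Z + 0.476| > 1.96) = 7.6%.
- b = 0.2, rho = 0.8: SE = 0.133, bias/SE = 0.753, giving 11.7%.
- b = 0.3: 11% and 20% at the same two correlations.

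**5. Same shift in both treatments.** The bias in the main contrast becomes b × [m1/(35 + m1) − m2/(35 + m2)], where m2 is the number choosing training. It is zero at 17/17. At 27/7 with b = 0.2 it is 0.2 × (27/62 − 7/42) = 0.05 SD. No such cancellation occurs in comparisons with the waiting list.

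**The case against.** The protocol names no model or analysis set that receives the crossover data. The main analysis is defined by group, the groups are the randomised arms, and the sample size counts no crossovers. A separate, labelled analysis would be compatible with the text, and an analysis plan not shown here might specify one. This stands, to the extent that a reader might infer that pooling into the primary analysis has been decided, and the protocol does not say so. It does not remove the point: the stated purpose leads towards pooling, and no other sentence limits it.

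A reader might also infer a flat contradiction with "in line with the intention-to-treat principle, all available randomized participant data will be analyzed". Waiting-list patients are randomised participants, and analysing their later data in their own arm breaks no rule. The conflict arises only if they are relabelled by the treatment they took.

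A third inference would be that the same people sit on both sides of the primary comparison. They do not, because the waiting list is on neither side of PIPCI versus active control. The overlap concerns only the waiting-list comparisons. There a random subject effect can handle the dependence between repeated measurements, but not the self-selection.

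Finally, preference, expectancy and repeat testing could act in both choices, so a shift confined to PIPCI choosers is an unfavourable assumption.

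**Conclusion.** The point holds as a fault in a stated purpose, not as proof that the primary analysis is compromised. The protocol plans non-randomised, later-treated follow-up in order to strengthen the efficacy evaluation, and it does not confine those data to a separate analysis. If they were pooled by treatment received, the effect estimate would lose the protection of randomisation and depart from intention to treat.

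The size cannot be known from the documents. Under an assumed 0.2 SD shift in PIPCI choosers alone, the nominal 5% test of the main contrast runs at about 6% (17/17) to 8% (34/0) with the shift in SDs of change. It reaches about 12% only in the extreme case of all 34 choosing PIPCI, the shift in outcome SDs and a correlation of 0.8. A reader might take that figure, or the 20% at 0.3 SD, as the expected inflation. The documents support neither the shift nor the split. With an equal shift and an even split the main contrast is unbiased. The design objection depends on none of these figures.

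The stated 93% with 35 per group does not rely on crossover data, so they are not needed to reach the planned power.

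**What to change.** Delete the power purpose from the Group 3 paragraph and state three things in the protocol.

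1. Primary and secondary between-group contrasts use participants as randomised. Waiting-list data up to and including the post-intervention assessment serve as the untreated control.
2. Data collected after a waiting-list patient takes up a treatment are reported separately as exploratory and non-randomised, for example as a within-person comparison of the waiting and treatment periods.
3. Because treatment is offered after the post-intervention assessment, the 6-month comparison with the waiting list is not against untreated patients. The claim of a maintained effect at 6 months therefore rests on PIPCI versus active control.

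The offer of treatment and the extra assessments can stay as they are. The cost is a few sentences and the loss of the apparent extra power (nominally 93% to about 98–99%). The third statement also narrows the main hypothesis, which now claims persistence against both controls. The sentence promising to analyse all available randomised data should be worded to fit the first two statements. All of this should be settled before outcome data are examined, so that whether to pool is not decided with results in view.

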#### Standardization of Procedures

The intervention manuals and additional materials will be available for all participating psychologists in a web-based encrypted forum. Adherence to the intervention manual is monitored by several study features: 1. Only psychologists with previous therapeutic experience in CBT/ACT will interact with patients. 2. Psychologists undergo intensive training on the intervention manual ahead of the intervention phase. 3. Regular supervision by experienced psychologists/psychotherapists. 4. An adherence checklist in the intervention manual, where the psychologist takes structured notes after each session. 5. Via randomized auditory recordings of the sessions that are reviewed by two independent clinical psychologists.

#### RCT Assessments

Data will be collected at pre-intervention (1 week before the interventions), post-intervention (1 week after the interventions) and 6 months follow-up (Figure 1). Blinded independent psychology graduated (MSc) assistants, psychology students under clinical training, or licensed psychologists will carry out the evaluation assessments to avoid biased estimates of treatment effects. Outcome analysis will be adjusted for pre-intervention baseline. Clinical data from the patients’ extended cognitive examinations will be extracted from their patient journals and statistically modeled to predict intervention outcomes.

**FIGURE 1 F1:**
[figure not shown]
Illustrating a CONSORT (Schulz et al., 2010) inspired flow-chart of the trial design. PIPCI, Psychological Intervention tailored for Patients with early Cognitive Impairment.

During pre-intervention assessments, data will be collected on demographics such as age, gender, education, employment status, and duration of cognitive complaints. In addition, the Childhood Trauma Questionnaire (CTQ) will be assessed to evaluate if early life trauma can predict treatment outcome (Bernstein et al., 2003).

During post-intervention assessments, data will be collected with the Client Satisfaction Questionnaire (CSQ) (Kwon et al., 2017) in order to evaluate the participant’s satisfaction with the interventions.

As recommended by the SPIRIT statement, a schematic overview of the timeline, and evaluation components is shown in Figure 2.

**FIGURE 2 F2:**
[figure not shown]
Illustrating a SPIRIT diagram of enrolment, intervention, and assessments. PIPCI, Psychological Intervention tailored for Patients with early Cognitive Impairment; MINI, Mini International Neuropsychiatric Interview; AAQ-II, Acceptance and action questionnaire – second version; PSS, Perceived Stress Scale; BDI, Becks Depression Inventory; BBQ, Brunnsvikens Brief Quality of Life Scale; SF-36, Short Form Health Survey; CWIT, Color Word Interference Test; TMT, Train Making Test; BVMT-R, Brief Visiospatial Memory Test Revised; AX-CPT, AX-Continuous Performance Task; D-LRTT, Deary-Liewald Reaction Time Task; ACTH, adrenocorticotropic hormone; DHEA, dehydroepiandrosterone; CTQ, Childhood Trauma Questionnaire; CSQ, Client Satisfaction Questionnaire.

### Outcome for the Pre- and Post-evaluations

#### Primary Outcome Measures

•Psychological health measures: Our primary outcome measure is psychological flexibility measured with the total score of the AAQ-II (Bond et al., 2011). This outcome is motivated by the fact that psychological flexibility is the essential target of our psychological intervention and has a strong history of evidence, as detailed in the introduction.

#### Secondary Outcome Measures

•Psychological health measures: Stress-related symptoms reported with the Perceived Stress Scale (PSS) (Lee, 2012), depressive symptoms with the Becks Depression Inventory (BDI) (Dozois et al., 1998), quality of life with the Brunnsviken Brief Quality of Life Scale (BBQ) (Lindner et al., 2016), and general health with the Short Form Health Survey (SF-36) (Ware, 2000).•Cognitive functions: Executive functions with the Color-Word Interference Test (CWIT) and the Trail Making Test (TMT) from Delis-Kaplan Executive Function System (D-KEFS) (Delis et al., 2001), non-verbal episodic memory with the Brief Visuospatial Memory Test-Revised (BVMT-R) (Benedict et al., 1996), attention/working-memory with Digit-Span from the Wechsler Adult Intelligence Scale (WAIS-IV) (Wechsler, 2008), and the computer-based AX-Continuous Performance Task (CPT) (Braver and Cohen, 2000), processing speed with Digit-Symbol from WAIS-IV (Wechsler, 2008), and psychomotor speed with the Deary-Liewald Reaction Time Task (D-LRTT) (Deary et al., 2011).•Biological health measures: Telomerase (the enzyme involved in maintaining telomere length, among other things) activity by modified real-time telomeric repeat amplification protocol (Hou et al., 2001). This outcome is motivated by previous research showing that biological measures, such as telomere length are related to aging and differences in such biological marker has been coupled with differences in the prevalence of psychiatric, cognitive, and somatic conditions (Han et al., 2019). Telomerase activity may also be associated with improvement to psychological treatment (Månsson et al., 2019). In addition, we will also evaluate saliva measures of cortisol, testosterone, adrenocorticotropic hormone (ACTH), and dehydroepiandrosterone (DHEA) (Kalman and Grahn, 2004).•Costs-effectiveness: Health-economic impact is measured in Quality Adjusted Life Years (QALY’s) (Torrance and Feeny, 1989).

#### Reliability and Validity of Outcome Measurements

For AAQ-II the mean alpha coefficient for the items is 0.84 and the scale has shown acceptable test-retest reliability (0.79–0.81) (Bond et al., 2011). PSS has repeatedly shown alpha coefficients of >0.70 and the test-retest reliability has been assessed in four studies and met the criterion of >0.70 in all cases (Lee, 2012). BDI-II has shown high internal consistency with alpha coefficient >0.90, furthermore, it has shown adequate validity in terms of diagnostic discrimination as well as validity in terms of factorial and content validity (Dozois et al., 1998). BBQ has shown satisfactory reliability both in terms of inter-item correlation and Cronbach’s alpha, as well as regarding test-retest reliability in the short term. An intra-class correlation coefficient of 0.82, indicate high test-retest reliability (Lindner et al., 2016). The SF-36 is a well-validated and reliable scale that often reaches alpha coefficients of >0.80, and has been used in multiple settings and shown both discriminatory and predictive ability (Ware, 2000). For the cognitive measures, information regarding reliability and validity are referred to in the test manuals above. For the biological measures, the analytical methods are yet to be decided, but we aim to employ methods with adequate psychometric properties.

### Power Estimation and Sample Size

No studies are available directly comparing CBT/ACT in a cognitively impaired population with an active control condition using AAQ-II. Therefore, we designed our RCT as a superiority trial with enough statistical power to detect a difference in outcome between treatments (if present) with a medium effect size. We chose this minimum difference because such a difference is important based on a patient’s perspective or clinical knowledge. Expecting larger differences in outcome does not seem realistic (Regan and Varanelli, 2013) and might result in an underpowered study while detecting smaller differences is of less relevance for clinical practice. The calculation is estimated on AAQ-II pre- and post-intervention change between the PIPCI group and the active control group Sample size was calculated with the R package SIMR, which allows power calculations of Linear Mixed Models (LMM) and is based on Monte Carlo simulations (Green and Macleod, 2016). The sample size estimate is based on changes in our primary outcome, AAQ-II. The model included the interaction of time (pre- versus post-test 1; continuous) and group (experimental versus active control; factor). The model also had a subject ID (factor) as a random effect to account for repeated measurements. We used the power curve function to explore trade-offs between power and sample size. The analysis showed that to get a significant difference between the experimental group and the active control group we need at least 35 participants (to have 93% power) in each group. We expect a 15% attrition rate (Norton et al., 2014), so initial recruitment of 120 (40 in each group) participants should ensure that about 105 participants remain in the final sample. The output of the power analysis is shown in Figure 3.

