### Hypotheses

#### Main Hypothesis

1.The main hypothesis states that participants receiving PIPCI will increase their psychological flexibility compared to participants in the active control group and the waiting list control group and that this effect will be maintained at 6 months follow-up.

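### The sample-size paragraph misses its own minimum by one per arm, leaves the inputs behind 93% power unstated, and powers one contrast of a wider main hypothesis

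*Protocol article*

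**What the plan says.** All references are to the protocol article.

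- **Power Estimation and Sample Size.** The trial is designed "to detect a difference in outcome between treatments (if present) with a medium effect size". The scope is stated: "The calculation is estimated on AAQ-II pre- and post-intervention change between the PIPCI group and the active control group". The simulated model is a linear mixed model: "The model included the interaction of time (pre- versus post-test 1; continuous) and group (experimental versus active control; factor"), with a random effect for subject. The result is that "we need at least 35 participants (to have 93% power) in each group". Attrition of 15% is expected, and "initial recruitment of 120 (40 in each group) participants should ensure that about 105 participants remain in the final sample".
- **Reliability and Validity of Outcome Measurements.** For the AAQ-II, "the scale has shown acceptable test-retest reliability", given as 0.79 to 0.81. This is the only figure in the article that bears on a pre-post correlation.
- **RCT Assessments.** Outcome analyses will adjust for the pre-intervention value.
- **Main Hypothesis.** PIPCI is to increase psychological flexibility compared with the active control group and "the waiting list control group and that this effect will be maintained at 6 months follow-up".
- **Strategy for the Main and Secondary Hypotheses Analyses.** The main analysis compares change between PIPCI and active control, with comparisons against the waiting list in addition. "An alpha level of 0.05 and a 95% CI will be used to evaluate the main and secondary analyses".

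**The concern.** Three things in or around the sample-size paragraph do not fit together.

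1. The number expected to remain does not follow from the recruitment number and the attrition rate, and the correct number lies below the minimum the paragraph sets.
2. A power figure is given to the percentage point, but neither the effect (in AAQ-II points or SD) nor the correlation between the two measurements is stated. For a test of change, the correlation drives the result.
3. The main hypothesis has two comparators and two time points. One of those four comparisons is powered, and the article does not say which result, or which combination, would confirm the hypothesis.

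At stake is how the result is read. A null result could be taken as good evidence against a medium effect when that depends on an undisclosed input. A single significant comparison among several could be presented as confirming the main hypothesis.

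**Working it through.** **Attrition**

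- Per arm: 40 x (1 - 0.15) = 34. Total: 120 x 0.85 = 102.
- The attrition that leaves 105: 1 - 105/120 = 12.5%.
- Recruitment that keeps 35 after 15% attrition: 35/0.85 = 41.2, so 42 per arm and 126 in total.

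**Power for PIPCI versus active control at post-intervention**

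Inputs from the article: 35 per arm, alpha 0.05, two time points, subject random intercept. Assumptions: alpha is two-sided (the 95% CI suggests it, but it is not stated); medium means d = 0.5 in raw AAQ-II SD units; the SD is equal at both times.

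With two time points and a random intercept, the time-by-group test is a comparison of mean change. With r the pre-post correlation, the SD of change is sqrt(2(1 - r)) in raw SD units, and power follows from the noncentral t with 2n - 2 degrees of freedom.

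The stated 93% cannot be reproduced directly, because d and r are not given. Solving backwards, 93% at 35 per arm needs a standardised difference in change of 0.833. Setting d/sqrt(2(1 - r)) = 0.833 gives r = 1 - (d/0.833)^2/2:

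- d = 0.4: r = 0.88
- d = 0.5: r = 0.82
- d = 0.6: r = 0.74

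Power at d = 0.5 by correlation:

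| r | 35 per arm | 34 per arm |
|---|---|---|
| 0.50 | 54% | 53% |
| 0.60 | 64% | 62% |
| 0.70 | 76% | 75% |
| 0.79 | 88.9% | 88.0% |
| 0.81 | 91.7% | 90.9% |
| 0.82 | 93.0% | 92.3% |

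The attrition slip alone therefore costs about 0.7 points at r = 0.82.

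With baseline adjustment as in ANCOVA, the SD becomes sqrt(1 - r^2). Then 93% at 35 per arm needs r = 0.80, and r = 0.79 to 0.81 gives 92% to 94%. At 34 per arm, ANCOVA power is 81% at r = 0.7 and 65% at r = 0.5.

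If medium instead meant 0.5 SD of the change score, power at 35 per arm would be 54% whatever the correlation.

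**Scope**

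| Comparison | Main hypothesis | Named main analysis | Powered |
|---|---|---|---|
| Active control, post | yes | yes | yes |
| Waiting list, post | yes | additional | no |
| Active control, 6 months | yes | time point not fixed | no |
| Waiting list, 6 months | yes | additional | no |

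**The case against.** The case for the plan is strong on several points.

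- **Attrition.** The remaining sample is given as approximate, and 102 is within 3% of 105. The planned maximum-likelihood analysis also keeps the baseline values of those who drop out, which recovers a little. This stands as to size. It does not remove the conflict with a minimum of 35.
- **The 93%.** A reader might infer that it is wrong because it needs a correlation above the quoted reliability. The article does not support that. The figure of 0.82 holds only for d = 0.5 raw SD. At that effect, the quoted reliability of 0.79 to 0.81 gives 89% to 92% by change score and 92% to 94% with the planned baseline adjustment, close to a stated value that is itself a Monte Carlo estimate. Figure 3 is not available here, and the full protocol may hold the inputs. The correlations of 0.5 to 0.7 are assumptions of this review, not figures from the article. What stands is narrower: test-retest reliability is a favourable stand-in for a correlation across a 10-week intervention with varying response, and power falls quickly as the correlation drops.
- **Scope.** A reader might infer that power is claimed for the whole main hypothesis. It is not: the sample-size section names its contrast and period, and the analysis section names the same two groups for the main analysis.
- **Error rates.** A reader might combine low joint power with an inflated type I error, but these belong to different success rules. If all four comparisons must succeed, there is no inflation; joint power at 34 per arm would be about 79% (r = 0.82) or 45% (r = 0.7), assuming 0.5 SD in each and equal correlations between visits. If any one suffices, type I error is about 9% over the two post-intervention comparisons and 16% over all four. The hypothesis joins its parts with 'and', which favours the first rule. The assumed 0.5 SD against the waiting list at 6 months is doubtful, because that group is offered an active intervention after the post-intervention evaluations (RCT Design and Groups).

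**Conclusion.** The concern holds in a limited form, of minor to moderate severity.

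- **Wrong as written:** 15% attrition from 40 per arm leaves 34 (102 in total), one per arm below the paragraph's own minimum. The cost is about 0.7 points of power, given d = 0.5 raw SD and r = 0.82.
- **Undocumented and sensitive, not shown to be false:** the 93% depends on an effect size and a correlation that the article does not state as numbers.
- **Not aligned:** the main hypothesis is wider than the contrast that is powered and named as the main analysis. The main analysis has no fixed time point there, and 0.05 applies to every comparison without an order.

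The power figures rest on two-sided 0.05, equal SDs and the random-intercept model as described.

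**What to change.** 1. In Power Estimation and Sample Size, replace about 105 with 102 completers (34 per arm) and report the simulated power at 34 per arm. The alternative of recruiting 42 per arm (126) would keep 35, but is not needed to make the text correct.
2. In the same paragraph, give the effect in AAQ-II points and in SD, say which SD, give the pre-post correlation used, and show power over a range such as r = 0.5 to 0.8.
3. Align Main Hypothesis with the analysis strategy: name PIPCI versus active control at post-intervention as the single primary test. Either test the waiting-list comparison at post-intervention and the active-control comparison at 6 months afterwards in a fixed order, each at 0.05 only if the one before is significant, or label them secondary. Label the waiting-list comparison at 6 months secondary, given the offer of active treatment to that group.

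The cost is a re-run of the simulation and a few sentences of wording, with no extra patients. The downside is that the stated power becomes slightly less favourable, and the range makes its dependence on the correlation visible.
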